| **4. Study protocol** |
| --- |
| 1. **Study population**   The study participants will be enrolled from the outpatient clinics of internal medicine department, family medicine department and Chinese medicine department of Linsen and Chinese medicine branch of Taipei City hospital.   1. **Study period**   2011/01/01 to 2012/12/31   1. **Study group**   2 groups   1. **Study duration**   16 weeks   1. **Study design**   Double blinded, randomized, and placebo-controlled trial   1. **Randomization**   The randomization sequence will be generated by a table of random numbers from the SPSS software. The allocator will have to call a central number to receive the next allocation sequence once a patient had been enrolled in the trial.   1. **Primary endpoint** 2. The percentage of change between baseline and 16 weeks in fasting triglyceride, total cholesterol, HDL, LDL. 3. Anthropometric measurements in terms of body weight, height, BMI, waist circumference, and hip circumference.   **8. Secondary endpoint**   1. The percentage of change between baseline and 16 weeks in fasting sugar, HbA1C, obesity related hormone peptides, such as leptin、adiponectin、ghrelin、fasting insulin resistance、APOB、APOA1, high sensitivity C-reactive protein (hsCRP) 2. HRQOL scores on the WHOQOL-BREF   Assessment method:  All measurements of biochemical characteristics and obesity-related hormone peptides of blood sample will be made at 0800-0900 after an overnight fasting using standardized methods. All measurements will do after an overnight fast using standardized method and will be performed in the beginning of the study and after 16 weeks of treatment. Height is measured with a wall-mounted stadiometer to the nearest 0.1 cm, weight is measured on a calibrated balance beam scale to the nearest 0.1 kg, and BMI is calculated according to the formula: BMI = body weight (BW) / height (kg/m^2^). We simultaneously collected the demographic data and fasting laboratory data such as blood sugar, creatinine, aminotransferases aspartate, aminotransferases alanine, uric acid, and plasma lipoproteins (triglyceride, cholesterol, HDL-cholesterol (HDL) and LDL-cholesterol (LDL)). Homeostasis model assessment for insulin resistance (HOMA-IR)【fasting glucose (mmol/l) × fasting insulin (UI/l)/22.5】 is used as insulin resistance measurement (25-26). All measurements will make at 0800-0900 after an overnight fast using standardized methods. A sample of whole blood was drawn and centrifuged at 4°C, and a 1-ml aliquot of serum was rapidly frozen (-80°C) for subsequent hormone analysis. The plasma adiponectin concentration will be measured by a radioimmunoassay kit (Linco Research, Inc., St. Charles, MO, USA). This kit employs the double-antibody/ polyethylene glycol technique using ^125^I-lableled adiponectin and a multispecies adiponectin rabbit antiserium. Plasma insulin levels will be measured using a commercially available radioimmunoassay (Linco Research, Inc., St. Charles, MO, USA). Plasma ghrelin levels will be measured with a commercially available radioimmunoassay (Linco Research, Inc., St. Charles, MO, USA), using ^125^I-lableled ghrelin as a tracer. The detection limitation for the assay will be 10 ng/ml.  **9. Safety evaluation**  （1）adverse event  （2）vital signs  （3）Physical examination  　 （4）laboratory evaluation including liver function and renal function  **10. Inclusion criteria**   1. Age between 20 and 65 years 2. Diagnosis of type 2 diabetes for more than one year 3. Body mass index (BMI) ≥ 18 kg/m2 and ≤ 30 kg/m2 4. Fasting triglyceride ≥ 150 mg/dl or fasting low-density-lipoprotein cholesterol (LDL) ≥ 100mg/dl 5. Willing to participate in and fill out questionnaires for this trial   **11. Exclusion criteria**   1. Serum alanine transaminase > 80 U/L 2. Serum creatinine > 1.8 mg/dl 3. Breast feeding or pregnancy 4. Heart failure, acute myocardial infarction, stroke, heavy injury 5. Any other conditions not suitable for trial as evaluated by the physician   **12. study protocol:**  All participants met the criteria will be asked to sign the informed consent form after letters explaining the purpose of the study sent to all the patients inviting their participation. Participants will be randomly allocated to receive a decaffeinated GTE EGCG (Group A) or a placebo (cellulose; Group B) for 16 weeks. Both experimental and placebo treatments were contained in the same opaque capsules, which will be administered by a blinded research assistant. Participants will be instructed to maintain an isocaloric diet and to continue their previous eating habits during the study period. Every four weeks, Participants will return to our clinics and report to the study center for adverse events and compliance assessment. Participants will be free to withdraw at any time. Throughout the study period, participants will be directed to continue taking the same dose of any prescribed hypoglycemic agents unless hypoglycemia or severe complications occurred, in which case they will be directed to reduce their dose immediately.  **13. Adverse event report**  We will assess any adverse event of the participants during the study and will discuss the necessary to drop out.  **14. Drop out/ withdraw criteria**   - 1. drug compliance < 60% or no willing to return during the study   2. pregnancy occurred during the study   3. major illness or hospitalization occurred during the study   4. the dose of antidiabetic or antihyperlipidemia medication changed during the study   5. not suitable to participant after doctor assessed during the study   6. lost of follow up or death   **15. Statistical analysis**   1. The data will be analyzed using SPSS software (version 17.0, Chicago, IL.) 2. Independent t-tests will be employed to examine the difference in anthropometrics, biochemical characteristics, obesity-related hormone peptides, and life-quality scores between EGCG group and placebo group. 3. Paired t-tests will be employed to examine the difference between before and after intervention for 16 weeks in both groups. 4. All p values will be two-tailed and α level of significance will be set at 0.05. 5. This study population will be “Intent to treat population” for analysis of therapeutic efficacy 6. The definition of ITT （Intent to treat population）is that participants take the study medication once.   **16. Preparation of samples and placebo**  Decaffeinated GTE was obtained by [name] from the Tea Research and Extension Station, Taoyuan County, Taiwan. It was extracted from dried leaves of green tea according to pre-set standard procedures. The decaffeinated GTE used in this study was standardized for several tea catechins in addition to EGCG. The placebo comprised pure microcrystalline cellulose. Capsules contained either 500 mg decaffeinated GTE extract or cellulose. This sample contains 57.12% EGCG (80.83% Total catechines.  [figure not shown]  （1）The machine was used to extract decaffeinated GTE.  [figure not shown]  （2）Placebo (B group) was made by cellulose. |

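### The lipid comparison uses entry lipid and lipid-drug status in neither the named allocation method nor the named test: a small loss of precision, recovered mainly by covariate adjustment

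*Protocol*

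**What the plan says.** Protocol item 6 (Randomization) has two sentences. One gives the source of the sequence: "The randomization sequence will be generated by a table of random numbers from the SPSS software". The other gives its release: "The allocator will have to call a central number to receive the next allocation sequence once a patient had been enrolled in the trial". Item 12 names the two arms without an allocation ratio. No block, block size or stratification factor appears anywhere, and nothing says that none is used.

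Item 7 sets the lipid endpoint: "The percentage of change between baseline and 16 weeks in fasting triglyceride, total cholesterol, HDL, LDL". Item 15 names the between-arm method: "Independent t-tests will be employed to examine the difference in anthropometrics, biochemical characteristics", and so on through the remaining outcomes, with no covariate.

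Two features of the population bear on this. Item 10 has two entry routes: "Fasting triglyceride ≥ 150 mg/dl or fasting low-density-lipoprotein cholesterol (LDL) ≥ 100mg/dl". Item 11 does not exclude users of lipid-lowering drugs, and item 14 lists as a ground for drop-out that "the dose of antidiabetic or antihyperlipidemia medication changed during the study". Treated patients are therefore expected in the trial.

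**The concern.** Entry route is tied to the outcome by the design itself. A patient selected because triglyceride exceeded a threshold will tend to show some fall in triglyceride at 16 weeks through regression to the mean, whatever the capsule contains. A patient who entered on LDL alone will not show that fall in triglyceride, but will tend to show one in LDL. Background lipid-drug use is a second plausible influence on lipid change.

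As written, neither the allocation nor the test uses this information, although both facts are available when the allocation call is made. Two things are at stake. The t-test leaves in its error term variation that a model could remove. And in the one trial actually run, the arms may differ visibly on a relevant factor, with no planned adjustment to answer the question that follows.

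**Working it through.** **Inputs.** The protocol gives two arms, two-sided α = 0.05, independent t-tests and percentage change as the lipid outcome (items 7, 12 and 15). It gives no sample size, SD, effect size or power, so there is no stated figure to reproduce. Everything below rests on assumed values: 1:1 simple allocation, total N as shown, and one binary factor.

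**Step 1: how often a factor is out of balance.** With prevalence p, the standard error of the difference in prevalence between arms is about √(4p(1−p)/N). At p = 0.5 this is 1/√N. The simulation lets arm sizes vary as simple allocation does.

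| N | SE | 15 points ÷ SE | ≥15 points, normal | ≥15 points, simulated | ≥20 points, simulated |
|---|---|---|---|---|---|
| 60 | 0.129 | 1.16 | 25% | 25% | 13% |
| 80 | 0.112 | 1.34 | 18% | 19% | 8% |
| 120 | 0.091 | 1.64 | 10% | 10% | 3% |

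Outside this range, a difference of 20 points or more occurs in 18–22% of trials at N = 40 and in under 1% at N = 200 (prevalence 30–50%).

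A 20-point imbalance in a factor worth 1 SD moves the observed arm difference by 0.20 × 1 = 0.20 SD. If the factor is worth 0.5 SD, the shift is 0.10 SD.

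**Step 2: arm sizes.** A 55:45 or worse split has exact binomial probability 52%, 43% and 32% at N = 60, 80 and 120. It costs little. At 44:36 the relative efficiency is 4 × 44 × 36 / 80² = 6336/6400 = 0.99.

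**Step 3: error rate and power.** Assumptions: N = 80, prevalence 40%, treatment effect 0.65 SD, unit residual SD, a factor worth b SD, blocks of 4 where stratified, and 8,000 simulated trials per cell (simulation error about 0.005 on power).

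| Allocation and analysis | Power, b = 1 | Power, b = 0.5 | Type I error, b = 1 | Type I error, b = 0.5 |
|---|---|---|---|---|
| Simple, t-test (as written, if unrestricted) | 0.73 | 0.79 | 0.051 | 0.052 |
| Stratified, t-test | 0.75 | 0.81 | 0.031 | 0.044 |
| Simple, adjusted | 0.81 | 0.80 | 0.053 | 0.051 |
| Stratified, adjusted | 0.82 | 0.83 | 0.052 | 0.051 |

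**Check by formula, b = 1.** Ignoring the factor inflates the outcome variance to 1 + b²·p(1−p) = 1 + 0.4 × 0.6 = 1.24.

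- Unadjusted non-centrality: (0.65/√1.24) × √80/2 = 2.61. Against a critical value of 1.99, power is 0.73.
- Adjusted non-centrality: 0.65 × √80/2 = 2.91, which gives power 0.82.
- Stratified allocation removes the factor from the true variance of the difference, but the t-test still estimates it with variance 1.24. The effective critical value becomes 1.99 × √1.24 = 2.22, and Type I error falls to about 0.03.

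The formula and the simulation agree.

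**The case against.** The strongest case on the other side is that nothing here is wrong. A reader might infer that the protocol commits to an unrestricted sequence. It does not: a random-number table can also produce blocks or stratum lists, block sizes are often withheld to protect concealment, and the absence of restriction is inferred from silence.

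A reader might also infer that chance imbalance biases the comparison or inflates false positives. The documents do not support that either. Simple allocation released centrally after enrolment is valid and unpredictable. The t-test's standard error already allows for chance imbalance, and its simulated error rate stays at 0.047–0.052 whether or not the factor matters. Both objections stand, and the point is limited accordingly.

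Three further objections carry weight:

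- **Drug use.** The outcome is change from baseline and lipid-drug dose is meant to stay constant, so stable treatment is largely reflected in the baseline value. Entry route is the better-founded factor. The document gives no figure for how far users and non-users would differ.
- **Size.** N, prevalence and factor strength are all assumed. At N = 200 the imbalance is minor.
- **Where the gain lies.** Adjustment delivers most of it without touching the allocation, and a statistical analysis plan, if there is one, could supply it.

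The last objection only partly answers the point. Item 15 names the unadjusted t-test as the method, so a plan with covariates would replace what the protocol fixes. Stratification cannot be added for patients already allocated.

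**Conclusion.** The point holds as a minor efficiency improvement, not as an error or a contradiction. As the protocol reads, information known at entry and linked to the lipid endpoints is used neither in allocation nor in analysis. The consequence is lost precision and possible imbalance in the realised sample.

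At the assumed N = 80, the gain in power from adjustment alone is about 0.81 − 0.73 = 0.08 if the factor is worth 1 SD. It is only 0.01 to 0.02 (simulation and formula) if the factor is worth 0.5 SD. Stratifying alone adds about 0.02 in either case. These figures rest on one binary factor at 40% prevalence and a treatment effect of 0.65 SD. A continuous baseline lipid value was not modelled, and the protocol supplies none of these inputs.

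**What to change.** **Main change (item 15).** For the between-arm lipid comparisons, replace the independent t-test with a linear model (ANCOVA) containing treatment, the baseline value of the lipid concerned and lipid-lowering drug use (yes/no). The baseline lipid is already measured. Drug use has to be recorded before allocation.

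**Secondary change (item 6).** Have the central service issue permuted blocks of varying size, concealed from the clinic and stratified by baseline triglyceride (below versus at or above 150 mg/dl) and lipid-lowering drug use. Keep both strata in the model whenever they are used in allocation, because stratifying and then applying the plain t-test makes it conservative. If blocks or strata are already in use, item 6 should say so and name the strata; block sizes can stay undisclosed.

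**Cost.** The analysis change costs only a few lines of text. The allocation change needs a new list at the central number and two extra fields at the call. Its downside is that both entry facts must be known and recorded correctly at that moment.

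### Nine unranked primary variables, height among them, are each tested at two-sided 0.05 with no success rule, so the primary conclusion has no controlled error rate (about 18-30% for the seven distinct endpoints if any one counts)

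*Protocol*

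**What the plan says.** Protocol item 7 (Primary endpoint) has two entries. The first is "The percentage of change between baseline and 16 weeks in fasting triglyceride, total cholesterol, HDL, LDL". The second is "Anthropometric measurements in terms of body weight, height, BMI, waist circumference, and hip circumference". Four lipids and five body measures make nine primary variables, and none is singled out. Percentage change is attached to the lipids only; no change measure is given for the body variables.

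Item 8, under the assessment method, derives BMI from the other two measurements: "BMI is calculated according to the formula: BMI = body weight (BW) / height", in units of kg/m².

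Item 15 (Statistical analysis) fixes the tests. Between groups: "Independent t-tests will be employed to examine the difference in anthropometrics, biochemical characteristics" and other outcomes. Within groups: "Paired t-tests will be employed to examine the difference between before and after intervention for 16 weeks in both groups". For all of them: "All p values will be two-tailed and α level of significance will be set at 0.05". The protocol gives no ordering of endpoints, no division of alpha, and no rule for how many primaries must be significant.

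**The concern.** A threshold of 0.05 controls the error of one test. With nine primaries and no stated success rule, it is not the error rate of the conclusion that the trial will draw. Any one of the nine falling below 0.05 could be reported as a positive primary result.

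Two entries make the list worse. Adults aged 20 to 65 (item 10) do not change height in 16 weeks, so a significant height difference could reflect only chance, measurement error or baseline imbalance. BMI is computed from weight and height, so it adds almost nothing to weight as a measure of response, yet it stands as a separate primary.

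**Working it through.** The protocol states no familywise error rate, power or sample size, so there is no figure of its own to reproduce.

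**Inputs.** From the protocol: 4 + 5 = 9 primary variables (item 7); two-sided 0.05 for each test (item 15). Assumed: the correlations between test statistics, and that any one significant primary counts as success.

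**1. How many distinct endpoints.** With height fixed, BMI at week 16 divided by BMI at baseline equals weight at week 16 divided by weight at baseline, because the height term cancels. Percentage change in BMI and in weight are then the same number. For absolute change, the BMI change is the weight change divided by height squared; the two tests are close but not identical, because height varies between patients. Removing height and counting weight and BMI once leaves 9 − 2 = 7.

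**2. Independent tests.** Chance of at least one false positive = 1 − 0.95^k.

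- k = 4 (lipids only): 1 − 0.8145 = 18.5%
- k = 7: 1 − 0.6983 = 30.2%
- k = 9: 1 − 0.6302 = 37.0%

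**3. Correlated tests.** Equicorrelated normal test statistics, two-sided cut-off 1.96:

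| Common correlation (assumed) | 4 lipids | 7 distinct | 9 as listed |
| --- | --- | --- | --- |
| 0 | 18.5% | 30.2% | 37.0% |
| 0.3 | 17.4% | 27.2% | 32.6% |
| 0.5 | 15.6% | 22.9% | 27.0% |
| 0.7 | 13.0% | 17.8% | 20.2% |

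A less uniform pattern was also tried for the seven: total cholesterol with LDL 0.7 to 0.8, pairs of body measures 0.3 to 0.5, and lipids with body measures 0.05 to 0.1 in size. It gives about 27-28%. The paired within-group tests in item 15 are not counted in any of these figures.

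**4. The opposite success rule.** If all nine had to be significant, there would be no inflation. But height has no true effect, so its test is significant with probability 0.05, and the chance of overall success could not exceed 5% however well the treatment worked.

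**5. Cost of adjustment.** A test with 80% power at 0.05 has a standardised effect of 1.96 + 0.84 = 2.80. At the first Holm step:

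- four endpoints: 0.05/4 = 0.0125, critical value 2.50, power Φ(2.80 − 2.50) = Φ(0.30) = 62%
- seven endpoints: 0.05/7 = 0.0071, critical value 2.69, power Φ(2.80 − 2.69) = Φ(0.11) = 54%

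**The case against.** The strongest reply is that multiplicity rules commonly sit in a statistical analysis plan, which is not shown here, and that an alpha of 0.05 is compatible with adjusted p values. It is fair that the protocol's silence does not prove that no adjustment was ever planned. But the nine-item primary list and the 0.05 for every p value are fixed in this protocol, and the protocol followed as written has the error rate shown above. Height as a primary endpoint is likewise the protocol's own entry.

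It may also be said that height is loose drafting, measured only so that BMI can be derived. That is plausible and makes the correction easy, but item 7 still lists it as primary.

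Three stronger readings are tempting and are not supported:

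- A reader might drop height alone and quote 1 − 0.95^8 = 33.7%. That treats weight and BMI as two independent chances, which they are not.
- A reader might call BMI an exact duplicate of weight. That holds for percentage change, which item 7 states only for the lipids. If week-16 values were compared, the two would differ, because height varies between patients.
- A reader might infer that the body measures are invalid as endpoints because "Participants will be instructed to maintain an isocaloric diet and to continue their previous eating habits during the study period", or because item 10 admits patients with a BMI as low as 18. Holding diet constant helps to isolate the effect of the supplement; neither provision is an error, and neither bears on multiplicity.

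**Conclusion.** The point stands. Nine unranked primaries at 0.05 each, with no success rule, leave the primary conclusion without a controlled error rate. If any one significant result counts, the rate is about 18-30% for the seven distinct endpoints and 37% for nine independent tests. Removing the body measures would not cure it, since the four lipids alone give about 13-19%. These figures rest on assumed correlations and on the any-one-counts rule; neither is in the protocol, so no single percentage should be quoted as the trial's error rate. The conclusion does not hang on the choice: every case for the seven or the nine is at least three and a half times the nominal 5%. Under the all-must-succeed rule the design fails the other way, because of height. The missing rule is therefore a defect on either reading.

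**What to change.** Before unblinding, do one of the following:

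- name one of the listed variables, for example one lipid, as the single primary endpoint at two-sided 0.05, and make the rest secondary; or
- keep several primaries and apply Holm across those retained at an overall two-sided 0.05.

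In either case delete height as an endpoint, keeping it as a baseline measurement for BMI, and do not count both weight and BMI as primary. Error control does not require every body measure to be demoted; Holm works with whichever ones stay.

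The change is protocol wording and needs no new data. Its cost is fewer routes to claim success. Under Holm, a test with 80% power at 0.05 has about 62% at the first step with four endpoints and about 54% with seven. A single lipid avoids that loss and holds the error rate at 5%. It has its own price: item 10 admits patients on triglyceride or LDL, so some may enter without the chosen lipid being raised.

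### Percentage change with unadjusted t-tests is a poor scale for hsCRP and, less so, HOMA-IR: per-arm means drift upward and power is lost, though the between-arm test stays valid

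*Protocol*

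**What the plan says.** Protocol item 8 (secondary endpoint) sets the scale: "The percentage of change between baseline and 16 weeks in fasting sugar, HbA1C, obesity related hormone peptides", continuing through leptin, adiponectin, ghrelin, insulin resistance, apolipoproteins and hsCRP. Insulin resistance is HOMA-IR, a product of two concentrations: "fasting glucose (mmol/l) × fasting insulin (UI/l)/22.5". Item 7 puts the primary lipid endpoints, triglyceride among them, on the same percentage scale.

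Item 15 (statistical analysis) sets the tests. Between arms: "Independent t-tests will be employed to examine the difference in anthropometrics, biochemical characteristics, obesity-related hormone peptides, and life-quality scores". Within arms: "Paired t-tests will be employed to examine the difference between before and after intervention for 16 weeks in both groups". The level is 0.05, two-sided.

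Item 15 does not say whether each t-test uses percentage change, raw change or week-16 values. It names no log scale, rank test or baseline covariate. The protocol gives no sample size, SD, correlation or expected effect for any marker.

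**The concern.** Percentage change is asymmetric: a doubling counts +100 and a halving −50. If one patient doubles and another halves, the average is (100 − 50)/2 = +25%, although the two moves cancel on a ratio scale (2 × 0.5 = 1). The more a marker fluctuates within a person, the further the arithmetic mean drifts above zero with no real change. The patients with low baselines who produce the largest percentages also inflate the SD.

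Two things are at stake. A per-arm mean percentage change can show a rise that did not happen, or hide a fall that did. And a t-test on that scale, with no use of the baseline, needs a larger true effect to detect a difference.

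**Working it through.** The protocol states no figure to reproduce. **Every SD, correlation, effect and sample size below is an assumption**, as are log-normality and 1:1 allocation.

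**Step 1: mean percentage change when nothing changes.** Let s be the SD of the log value and ρ the correlation between log baseline and log week 16. Then SD of log change = s·√(2(1−ρ)), and expected percentage change = 100·(exp(SD²/2) − 1). If w is the within-person log-SD, SD = w√2, so the same quantity is 100·(exp(w²) − 1).

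| Marker type | Assumed input | SD of log change | SD²/2 | Mean % change, no true change |
|---|---|---|---|---|
| hsCRP-like | s 0.9, ρ 0.7 | 0.697 | 0.243 | +28% |
| hsCRP-like | w 0.6 | 0.849 | 0.360 | +43% |
| hsCRP-like | s 1.1, ρ 0.6 | 0.984 | 0.484 | +62% |
| HOMA-IR-like | s 0.6, ρ 0.7 | 0.465 | 0.108 | +11% |
| HOMA-IR-like | w 0.45 | 0.636 | 0.2025 | +22% |
| Triglyceride-like | s 0.5, ρ 0.65 | 0.418 | 0.0875 | +9% |
| Leptin-like | s 0.7, ρ 0.85 | 0.383 | 0.0735 | +8% |
| Ghrelin-like | s 0.4, ρ 0.7 | 0.310 | 0.048 | +5% |

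Within-person variation drives the result, not skewness across patients: the leptin-like marker is more spread out than the first HOMA-IR-like one but drifts less, because its ρ is higher.

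The drift can also mask a real fall. With w = 0.6, an active arm with a true 30% reduction has an expected mean percentage change of 100·(0.70 × 1.433 − 1) = +0.3%.

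**Step 2: type I error, simulated at 50 per arm with no effect.** The between-arm t-test on percentage change rejects in 4.5% to 4.9% of trials for the hsCRP-, HOMA-IR-, leptin- and ghrelin-like markers, because both arms carry the same drift. A one-arm test of percentage change against zero, in the settings given by s and ρ, rejects in 47% to 67% (hsCRP-like), about 27% (HOMA-IR-like), 20% (leptin-like) and 15% (ghrelin-like). A paired t-test on raw before and after values stays at about 4% to 5%.

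**Step 3: power at 50 per arm with a fixed effect.** Between-person and within-person log-SDs are 0.9 and 0.6 (hsCRP-like) and 0.6 and 0.45 (HOMA-IR-like). Repeat runs differ by one to three points.

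| Marker type, true reduction | Raw change | % change | Log change | Log-ANCOVA |
|---|---|---|---|---|
| hsCRP-like, 30% | about 25% | about 43% | about 56% | about 62% |
| HOMA-IR-like, 22% | about 32% | about 43% | about 49% | about 57% |

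For the hsCRP-like marker, the step from percentage to log change gives 56 − 43 = 13 points and baseline adjustment a further 62 − 56 = 6. For the HOMA-IR-like marker the split is 49 − 43 = 6 and 57 − 49 = 8.

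**Step 4: sensitivity, with the effect set to give about 80% power on log change (50 per arm).**

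| Marker type | Raw change | % change | Log change | Log-ANCOVA |
|---|---|---|---|---|
| hsCRP-like, s 1.1 | 36% | 61% | 79% | 87% |
| hsCRP-like, s 0.9 | 46% | 71% | 80% | 86% |
| HOMA-IR-like, s 0.6 | 62% | 76% | 80% | 86% |
| Leptin-like | 55% | 75% | 79% | 81% |
| Ghrelin-like | 70% | 79% | 81% | 86% |

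The loss due to the percentage scale alone is about 9 to 17 points (hsCRP-like), 5 (HOMA-IR-like), 3 (leptin-like) and 1.5 (ghrelin-like). The pattern does not hinge on 50 per arm. With the effect re-set each time, the hsCRP-like marker with s = 0.9 gives 70% against 80% at 40 per arm, and 69% against 79% at 100.

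**The case against.** The strongest reply is that the randomised comparison is valid. That stands. A reader might infer that this plan could produce a spurious treatment effect; it does not, since the drift is common to both arms and the type I error holds.

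Second, the protocol never says that it will report an arithmetic mean percentage change, and the within-arm paired test reads most naturally as raw before against after, where no spurious rise occurs. This also stands, as a limit. The per-arm drift arises only if percentage change is averaged, which is what a t-test on the item 8 endpoint compares. Reading the tests as raw change does not rescue the plan, because power is then lower still.

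Third, transformations and covariates are commonly left to a statistical analysis plan, so their absence alone is no fault. Agreed. The point rests on what the protocol does fix: the percentage endpoint and the t-test.

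Fourth, a reader might infer that all the skewed markers are badly affected. The figures do not support that for leptin or ghrelin, and no figure was worked out for adiponectin. Standardised fasting samples at a fixed hour (item 8), and exclusion or withdrawal for major illness (items 11 and 14), may also reduce within-person variation below the values assumed here.

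**Conclusion.** The point holds in a limited form. Percentage change with unadjusted t-tests is a poor choice for hsCRP and, to a lesser degree, HOMA-IR. It distorts per-arm averages and costs power, and part of the power available from log-ANCOVA comes from using the baseline rather than from removing skew. For leptin- and ghrelin-like markers the effect of scale is small. The between-arm test is not invalid, and these are secondary endpoints. The sizes rest wholly on assumed inputs, but the direction does not depend on their exact values, and the log-scale analysis did better in every hsCRP-, HOMA-IR-, leptin- and ghrelin-like setting tried, whichever scale the t-tests were meant to use. The change is worth making because it costs so little.

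**What to change.** In item 15, for hsCRP, insulin and HOMA-IR, and the hormone peptides:

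- compare arms by ln(week 16) with ln(baseline) as covariate;
- report the ratio of geometric means with its 95% CI, expressed as a percentage difference, which keeps the percentage reading that item 8 wants;
- summarise each arm by geometric mean ratio or median, not by arithmetic mean percentage change;
- state the scale for any t-test that is kept.

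For consistency, treat triglyceride in item 7 the same way.

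The cost is wording only, since baseline and week-16 samples are already planned. One small downside: values below an assay limit need a stated substitution before logs are taken.

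### HOMA-IR is an efficacy endpoint in all dosed patients, yet insulin users may enrol and in them it is not a valid measure of insulin resistance

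*Protocol*

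**What the plan says.** All references are to the protocol, section 4.

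- **Endpoint (item 8).** The secondary list opens with "The percentage of change between baseline and 16 weeks in fasting sugar, HbA1C, obesity related hormone peptides" and includes "fasting insulin resistance" as one of its entries.
- **Index (item 8, assessment method).** HOMA-IR, computed as fasting glucose times fasting insulin over 22.5, "is used as insulin resistance measurement".
- **Assay (item 8, assessment method).** "Plasma insulin levels will be measured using a commercially available radioimmunoassay". No measure of the patient's own secretion, such as C-peptide, is mentioned.
- **Entry (item 10).** "Diagnosis of type 2 diabetes for more than one year", with no limit on the type of glucose-lowering treatment.
- **Exclusions (item 11).** Four specific grounds: raised ALT, raised creatinine, pregnancy or breast feeding, and cardiac disease, stroke or major injury. The fifth is a discretionary clause: "Any other conditions not suitable for trial as evaluated by the physician". None names insulin.
- **Background treatment (item 12).** Patients are told to "continue taking the same dose of any prescribed hypoglycemic agents", apart from a stated exception for hypoglycaemia or severe complications. Insulin is not set apart from other agents.
- **Analysis (item 15).** Two-sample t-tests between the groups, in all who took study medication at least once. No endpoint has a narrower population.

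**The concern.** HOMA-IR is a product: for a given fasting glucose, a higher fasting insulin is scored as more resistance. That reading works only if the measured insulin is what the patient's own pancreas secreted in response to that glucose. In a patient who injects insulin, the plasma concentration may also depend on the dose, the product and the time since the last injection. A change in the index over 16 weeks then cannot be read as a change in resistance.

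Read together, the eligibility, background-treatment and analysis items place such values in the HOMA-IR comparison. At stake is one secondary endpoint: a real effect on resistance could be diluted or lost in noise, and the reported mean would mix two different quantities. The primary lipid and anthropometric endpoints are not touched.

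**Working it through.** The protocol states no sample size, SD, effect size or share of insulin users, so there is no figure to reproduce. The check has two parts.

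**1. Can insulin-treated patients reach the HOMA-IR analysis?**

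- Entry: item 10 asks for established type 2 diabetes and says nothing on treatment type.
- Exclusion: none of the four specific grounds in item 11 concerns insulin. The fifth leaves it to the physician.
- During the trial: item 12 covers any prescribed agent and keeps it going. The withdrawal rule in item 14 concerns a change of dose, not the type of agent.
- Analysis: item 15 takes everyone dosed once.
- Sampling: item 8 fixes an overnight fast and a morning hour, but not the interval since the last injection.

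The answer is yes at every step.

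**2. How much could it matter?**

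Inputs, all assumed because the protocol gives none:

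- a share f of patients on insulin, equal in both arms, with f = 0.1 or 0.2 for illustration;
- a true mean difference d in the other patients;
- no treatment signal in the insulin users;
- the same SD, s, in both kinds of patient;
- m patients per arm.

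All patients: the mean difference is (1-f)·d, so the test signal is (1-f)·d·√(m/2)/s.

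Patients not on insulin only: the difference is d, but each arm has (1-f)·m patients, so the test signal is √(1-f)·d·√(m/2)/s.

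Ratio, restricted to all: √(1-f)/(1-f) = 1/√(1-f).

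| f | Effect kept, all patients (1-f) | Total n multiplier, all patients 1/(1-f)² | Total n multiplier, restricted 1/(1-f) | Net gain in test signal 1/√(1-f) |
|---|---|---|---|---|
| 0.1 | 0.90 | 1/0.81 = 1.23 | 1/0.9 = 1.11 | 1/0.949 = 1.05 |
| 0.2 | 0.80 | 1/0.64 = 1.56 | 1/0.8 = 1.25 | 1/0.894 = 1.12 |

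The multipliers are relative to a trial with no insulin users.

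The zero-signal assumption is the worst case for signal. If insulin users keep a fraction g of the effect, the all-patient difference is (1-f+fg)·d. Restriction then gains test signal only if √(1-f) > 1-f+fg, that is, if g < 1-(1-√(1-f))/f:

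- f = 0.1: 1-0.0513/0.1 = 0.49;
- f = 0.2: 1-0.1056/0.2 = 0.47.

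So with equal SDs, restriction gains test signal if insulin users show less than about half of the effect. Above that it costs a little, and the case for it rests on the meaning of the index. If injection timing and dose inflate the SD in insulin users, the balance moves towards restriction.

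**The case against.** **The problem may not arise.** The protocol never says that an insulin user will enrol, and the discretionary exclusion could be used to keep them out. This stands as a limit on size: with f near zero there is little effect. It does not cure the text, because nothing ties that clause to insulin.

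**An endpoint-specific subset is ordinary SAP content.** A SAP may well restrict this analysis, and none is at hand. But eligibility, index, assay and efficacy population are all fixed in the protocol, and the point concerns how they combine. Followed as written, the protocol includes these patients.

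**Some information survives.** Fasting glucose is still in the product, the endpoint is a within-patient change, sampling is at a fixed hour, and doses are meant to stay constant. This stands. It is wrong to say that the values carry no information; they are not valid as a measure of resistance. The zero-signal figures are therefore a bound.

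Three stronger readings are tempting, and the documents do not support them:

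- *Fasting insulin is itself a named endpoint.* Item 8 lists insulin resistance and describes insulin as an assayed quantity. Insulin could fall under the open list of hormone peptides, but it is not named there.
- *The assay will measure injected insulin.* That depends on cross-reactivity and on the insulin product, and neither is specified. Whether it is detected fully, partly or not at all, the index loses its usual interpretation.
- *The comparison is biased between arms.* An uneven split of insulin users under randomisation is chance imbalance, which the test's error rate already covers. One could construct a treatment-related route through the dose reductions that item 12 allows. But item 14 makes a dose change a ground for withdrawal, and the protocol does not say whether later values from such patients count. That route is conjecture.

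**Conclusion.** The point holds as a small, inexpensive improvement to one secondary endpoint. As written, the protocol lets insulin-treated patients into the HOMA-IR comparison, where the index is not a valid measure of resistance. The harm is dilution, noise and loss of meaning.

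A reader might take the 10% or 20% shrinkage of the effect as the gain from the fix. It is not, because leaving those patients out also costs sample size. The net gain in test signal is about 5% for f = 0.1 and 12% for f = 0.2. This rests on assumed values of f, no signal in insulin users, equal SDs and equal shares in the arms. Any excess variance in insulin users would add to the gain; retained signal would reduce it. As the protocol gives no share of insulin users, the true size cannot be stated.

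**What to change.** Add a field for insulin use at baseline to the case report form, and one sentence to item 15 or the SAP. HOMA-IR, and fasting insulin if it is reported as an outcome, is analysed in randomised patients not on insulin at baseline, with the all-patient result as a sensitivity analysis. All other endpoints keep every patient.

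Define the subset by status before randomisation, not by insulin use during the 16 weeks. The comparison then remains randomised, and treatment cannot influence who is in it.

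The cost is a fraction f fewer patients for this endpoint, and a result that applies only to patients not on insulin. Eligibility and clinical management do not change.
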